##### Fatigue

The MFI 20 (Multidimensional Fatigue Inventory) questionnaire consists of 20 questions divided into four dimensions (Gentile et al., 2003): general and physical fatigue, mental fatigue, the reduction of activities and lack of motivation. Patients will answer questions by circling a number between 1 (“yes it is true”) and 5 (“no, it is not true”) that best applies to what they felt the previous days Administration of the questionnaire. High values indicate a high level of fatigue. This questionnaire appears to be relevant for measuring patient fatigue as it measures the three components of fatigue: physical, psychological and cognitive.

##### Anxiety-Depression

The presence of anxiety and depression symptoms will be measured by the HADS (Hospital Anxiety and Depression Scale) questionnaire (Zigmond and Snaith, 1983). This 14-item scale is used to calculate a standardized anxiety and depression score (0–100).

##### Physical Activity and Sedentary Behavior

Physical activity and sedentary behavior will be measured using the short version of the IPAQ (International Physical Activity Questionnaire) (Craig et al., 2003). This self-administered questionnaire measures the practice of physical activity over the previous 7 days in terms of frequency (number of times per week), duration (number of hours and/or minutes in each session) and intensity (intense, moderate and walking). The combination of these 3 parameters will make it possible to calculate an energy expenditure score related to physical activity in MET-min/week from the (IPAQ Research Committee, 2005). sedentary behavior will be measured by the average time spent sitting per day and according to the context (TV, computer and total time).

#### Qualitative Data

Individual retrospective narrative interviews with 10 patients to question the experience, the difficulties and levers, as well as the adaptations made to the programme, in order to identify the indicators of effectiveness and the necessary adaptations.

### Data Management

#### Data Management Quality Control

Data will be collected and storied in a secure server of the CHRU de Nancy (CIC-1433 EC) using Ennov^®^.

#### Outcomes

The primary outcome is the evolution of QoL score. Secondary outcomes are disability score, fatigue, anxiety-depression, cost-effectiveness and process evaluation.

### Sample Size

The 2 fencing halls have a maximum capacity of 24 patients per year (12 patients per hall). The results of this pilot study will be used to refine the number of subjects needed for the main clinical trial. Nevertheless, with the number of patients to be included, setting an alpha risk of 5%, a power of 80% and assuming normality of the distribution of the QoL score with a standard deviation of 10 points, we will be able to detect a minimum difference in QoL evolution of 8.26 points between the two groups.

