**Methods and analysis:**

This is a prospective randomized controlled trial including 24 patients with invasive BC who have just undergone surgery. The study will be proposed to the patient and if interested, the patient will be referred to a sports physician for a medico-sportive evaluation. At the end the evaluation, if the patient meets the inclusion criteria, she will be randomly assigned to one of the 2 groups based on a 1:1 principle: *Early RIPOSTE group* (receive one fencing session per week for 3 months immediately after their inclusion), *Delayed RIPOSTE group* (receive one fencing session per week for 3 months but within the 3 months following their inclusion). Patients will be included for 6 months with 3 follow-up times (0, 3, and 6 months) by a sport physician. The primary outcome is the evolution of quality of life score. Secondary outcomes are disability score, fatigue, anxiety-depression, cost-effectiveness and process evaluation.

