### Recruitment and Randomization

The study is to be initiated from September 2021 with an anticipated end for subject recruitment in November 2021. Study completion is scheduled for June 2022.

The study will be proposed to the patient by the oncologist or surgeon after surgery. If interested, the patient will be referred to a sports physician for a medico-sportive evaluation. At the end the evaluation, if the patient meets the inclusion criteria, she will be randomly assigned to one of the 2 groups based on a 1:1 principle using automatic software Ennov^®^ (Figure 1):

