### Statistical Analysis

#### Quantitative Analysis

The primary analysis will be performed according to the intention-to-trait principle by comparing the 6-month average evolution of quality of life score between the two groups using mixed model for repeated data. The main criterion of the programme's effectiveness will be assessed by comparing average changes in the 6-month quality of life score between the two groups. An analysis of the missing data will be carried out and the randomness or otherwise of the missing data will be investigated (Diggle and Rubins classification). For the main analysis, a distinction will be made between two types of analysis:

Univariate analysis allowing the comparison of differences in quality of life scores between the two arms: non-parametric (Mann Whitney-Wilcoxon) and/or parametric (Student Test) methods.Multivariate analysis of the repeated customized analysis of variance type taking into account the adjustment and stratification variables (mixed models with consideration of repeated measurements and random center effects). These models make it possible to use not only the measurements at the two extreme times (M0 and M6) but also to take into account the measurement at the intermediate time (M3). They also make it possible to take into account the random center effect (the same intervention will not always have the same effect from one center to another). The SAS MIXED or GLIMMIX procedures will allow this analysis.

Other comparisons will use the same statistical methods for secondary judging criteria.

An analysis of the 6-month change profiles of the different dimensions of quality of life taking into account all monitoring times (0, 3, and 6 months) will be carried out using the Latent Class Growth Analysis (LCGA) methods (Jones et al., 2001; Jung and Wickrama Ka, 2008). This method makes possible to identify sub-groups of patients with distinct trajectories of progression within the entire sample. A comparison of the distribution of these trajectories will be made according to the intervention group.

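### The detectable difference of 8.26 points belongs to 24 patients per group; with the planned 12 per group it is about 12.0 points, and power at 8.26 is about 49%

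*Protocol article*

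**What the plan says.** The Abstract (Methods and analysis) fixes the size: "This is a prospective randomized controlled trial including 24 patients with invasive BC who have just undergone surgery". The Sample Size section explains that this number comes from the capacity of two fencing halls, 12 patients each per year. Under Recruitment and Randomization, an eligible patient is allocated so that "she will be randomly assigned to one of the 2 groups based on a 1:1 principle". That makes 12 patients per group.

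The Sample Size section then makes one quantitative claim. It takes an alpha of 5% and a power of 80%, "assuming normality of the distribution of the QoL score with a standard deviation of 10 points", and concludes that "we will be able to detect a minimum difference in QoL evolution of 8.26 points between the two groups". It gives no per-group number, sidedness, test, correlation between time points or allowance for dropout.

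Under Quantitative Analysis, the two-group comparison of differences in score is to use "non-parametric (Mann Whitney-Wilcoxon) and/or parametric (Student Test) methods", alongside a mixed model over months 0, 3 and 6.

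**The concern.** For two groups of 12 with an SD of 10, a detectable difference of 8.26 points looks too small. The standard error of the difference between two means is then about 4.1 points, and 80% power needs a true difference of nearly three standard errors. A figure of 8.26 is only about two.

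There is a second, linked difficulty. The SD of 10 is described as that of the quality-of-life score, but the difference is one in its evolution. The SD of a change equals the SD of a single score only at one particular correlation between the two measurements.

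This is the only operating characteristic that the article gives. The main objective is a formal comparison of the two groups, so the sentence tells readers what that comparison can find. If it is wrong, they are told that the trial has an 80% chance of finding a difference that it would miss about half the time.

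**Working it through.** **Inputs**

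- Total 24 patients (Abstract; Sample Size), allocated 1:1 (Recruitment and Randomization): n = 12 per group.
- Alpha 5%, power 80%, SD 10 points (Sample Size).
- Two-sided testing is assumed, because sidedness is not stated; one-sided testing is also tried.
- Student t test (Quantitative Analysis), with 10 taken first as the SD of the quantity compared.

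**Formula**

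With n per group, the standard error is SE = SD × √(2/n), with 2n − 2 degrees of freedom. Power is the probability that a noncentral t variable with noncentrality d/SE exceeds the two-sided 5% critical value. The detectable difference is the d that gives 80%.

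**Reproducing the stated figure: n = 24 per group**

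- SE = 10 × √(2/24) = 2.887; 46 degrees of freedom; critical t = 2.013.
- Solving for 80% power gives d = 8.261.
- Power at 8.26, with noncentrality 8.26/2.887 = 2.861, is 79.99%.

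This matches the article to two decimals, but it is a trial of 48 patients.

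**The planned trial: n = 12 per group**

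- SE = 10 × √(2/12) = 4.082; 22 degrees of freedom; critical t = 2.074.
- Solving for 80% power gives d = 11.968, and 11.968/8.26 = 1.45, so 45% larger.
- Power at 8.26, with noncentrality 8.26/4.082 = 2.023, is 49.0%.

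**Other readings at 12 per group**

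| Method | Detectable difference | Power at 8.26 |
|---|---|---|
| t test, two-sided | 11.97 | 49.0% |
| Normal approximation, two-sided | 11.44 | 52.5% |
| t test, one-sided | 10.48 | 62.4% |
| Normal approximation, one-sided | 10.15 | 64.7% |
| Mann-Whitney, two-sided (asymptotic efficiency 3/π, normal approximation) | 11.70 | not computed |

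None of these gives 8.26. The two-sided normal approximation also returns 8.261 at 23 per group, but that size appears nowhere in the article and is again about twice the planned one.

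**If 10 is the SD of a single score**

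With equal variances at both times and correlation ρ between months 0 and 6, the SD of the change is 10 × √(2(1 − ρ)). After adjustment for baseline the SD is 10 × √(1 − ρ²). The article gives no ρ, so the values below are assumptions that show the range (two-sided t test, 12 per group).

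| ρ | SD of change | Detectable, change score | Detectable, baseline-adjusted |
|---|---|---|---|
| 0.3 | 11.83 | 14.2 | 11.4 |
| 0.5 | 10.00 | 12.0 | 10.4 |
| 0.7 | 7.75 | 9.3 | 8.5 |

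To reach 8.26 with 12 per group, the SD of the quantity compared would have to be 10 × 8.26/11.968 = 6.90. That requires ρ = 1 − 0.690²/2 = 0.76 for change scores, or ρ = √(1 − 0.690²) = 0.72 with baseline adjustment.

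**Dropout**

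The article states no attrition rate. As an illustration, with SD 10 for the quantity compared, 11 evaluable patients per group gives 12.6 points and 10 per group gives 13.2.

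**The case against.** Four points can be made for the plan.

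- **It is a pilot.** Its size follows from hall capacity and not from 8.26 points. The article lists the small sample as a limitation and leaves real effectiveness to a larger trial. This stands, and it is why no change to enrolment follows. But a general caveat about size does not correct a specific figure that is wrong.
- **The primary analysis is a mixed model.** It uses month 3 and could be more precise than a t test on change scores. The values of 12.0 points and 49% therefore belong to the unadjusted comparison with SD 10, and should be quoted with that condition. This does not rescue 8.26: the gain needs a correlation of about 0.72 to 0.76, none is stated, and the match at 24 per group makes an unstated gain in precision an unlikely source.
- **The cause is inferred.** No formula is given, so the entry of the total as the per-group size is probable and not documented. The error in the figure does not depend on how it arose.
- **Misuse of the figure is conjecture.** Nothing in the article says that a null result will be read as excluding 8 points, or that 8.26 will be reused; it is the pilot's results that are to refine the size of the main trial. This is fair, and the finding does not rely on either.

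**Conclusion.** The concern holds. For 12 patients per group, two-sided 5%, 80% power and an SD of 10 for the change compared, the detectable difference is 11.97 points, not 8.26, and power at 8.26 is 49%, not 80%. The stated figure is that of a trial twice the planned size.

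The result rests on two assumptions: a two-sided test, and 10 as the SD of the compared change, which is also the assumption under which 8.26 reproduces. One-sided testing lowers the detectable difference to 10.48 points. If 10 is instead the SD of a single score, an unadjusted change-score comparison gives 14.2, 12.0 or 9.3 points for assumed correlations of 0.3, 0.5 or 0.7. The arithmetic is certain; only the cause is inferred. It must be corrected, because it is the article's only statement of what the trial can detect and nothing elsewhere in the article corrects it.

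**What to change.** Restate the sentence in the Sample Size section along these lines: with 12 patients per group, a two-sided alpha of 5%, 80% power and an SD of 10 points for the change from month 0 to month 6, the detectable difference between groups is 12.0 points; power for a difference of 8.26 points is about 49%.

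Say explicitly that 10 is the SD of the change, as the calculation treats it. If the sponsor meant the SD of a single score, the sentence should give the assumed correlation between months 0 and 6 and the detectable difference recomputed from it.

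The figure of 8.26 should not be carried into the trial report or into planning of the main trial.

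The cost is one corrected sentence and a less favourable figure. Enrolment, design and analysis stay as they are.

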### Statistical Analysis

#### Quantitative Analysis

The primary analysis will be performed according to the intention-to-trait principle by comparing the 6-month average evolution of quality of life score between the two groups using mixed model for repeated data. The main criterion of the programme's effectiveness will be assessed by comparing average changes in the 6-month quality of life score between the two groups. An analysis of the missing data will be carried out and the randomness or otherwise of the missing data will be investigated (Diggle and Rubins classification). For the main analysis, a distinction will be made between two types of analysis:

Univariate analysis allowing the comparison of differences in quality of life scores between the two arms: non-parametric (Mann Whitney-Wilcoxon) and/or parametric (Student Test) methods.Multivariate analysis of the repeated customized analysis of variance type taking into account the adjustment and stratification variables (mixed models with consideration of repeated measurements and random center effects). These models make it possible to use not only the measurements at the two extreme times (M0 and M6) but also to take into account the measurement at the intermediate time (M3). They also make it possible to take into account the random center effect (the same intervention will not always have the same effect from one center to another). The SAS MIXED or GLIMMIX procedures will allow this analysis.

Other comparisons will use the same statistical methods for secondary judging criteria.

An analysis of the 6-month change profiles of the different dimensions of quality of life taking into account all monitoring times (0, 3, and 6 months) will be carried out using the Latent Class Growth Analysis (LCGA) methods (Jones et al., 2001; Jung and Wickrama Ka, 2008). This method makes possible to identify sub-groups of patients with distinct trajectories of progression within the entire sample. A comparison of the distribution of these trajectories will be made according to the intervention group.

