## Methods and Analysis

### Design of RIPOSTE Trial

A prospective randomized controlled trial including patients with invasive BC who have just undergone surgery from 3 centers in Northeastern France (CHRU Nancy, Institut Lorrain de Canérologie and HIA Legouest Metz). The study will be proposed to the patient by the oncologist or surgeon after surgery. If interested, the patient will be referred to a sports physician for a medico-sportive evaluation.

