### Interventions

Once a week, for a duration of 1–1.5 h/session, and during a complete sport season, a group of 10–12 patients practiced adapted fencing. Following a warm up time dedicated to muscle awakening and progressive cardio-respiratory solicitation, patients then started specific fencing exercises from fundamental footwork (advance, retreat, lunge) to actions involving the injured side that holds the saber. Fencing is adapted in so far as all offensive and defensive actions are performed with respect of the mobility of the shoulder. Primary (tierce = outside; quarte = inside; quinte = head) and secondary parries are therefore executed by patients with the highest mobility but without ever causing pain. Coordination, agility and strength are trained during exercises between patients and during lessons with the fencing master. The adapted fencing session finished with a cool down period and a final salute.

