#### Month 6 Visit

This last visit will be devoted to the collection of follow-up data at 6 months (medico-sportive evaluation and administration of questionnaires). If patients do not attend this follow-up visit, a de-identified questionnaire will be sent to the patients' homes within 2 weeks in a pre-stamped, stamped envelope addressed to CIC-1433 EC.

A random selection of 10 patients, 5 from each intervention group, will be contacted by phone to obtain their agreement to participate to the qualitative investigation. An appointment will be made for a retrospective narrative interview at their convenience. It will enable the participants to question their experiences, difficulties and levers, as well as the adaptations made to the programme, in order to identify the indicators of effectiveness and the adaptations necessary for adherence and greater effectiveness of the programme. This interview will be carried out face-to-face by a researcher from the project team.

Two semi-structured interviews of the 2 fencing master will be carried in order to assess the effectiveness indicators, in particular the acceptability of the patients (profiles remaining committed), the difficulties encountered (technical, social, psychological, etc.), the levers (posture, resources, support) and the necessary adaptations (pedagogy, gestures, technique) for better commitment and effectiveness.

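### Three centres and 24 patients are too few to estimate usefully a random centre effect described as an intervention effect that varies by centre

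*Protocol article*

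**What the plan says.** All places are in the Protocol article. Quantitative Analysis lists, as part of the main analysis, a repeated-measures mixed model with random centre effects, to be fitted in SAS MIXED or GLIMMIX. It explains that these models "take into account the random center effect (the same intervention will not always have the same effect from one center to another". The same section also lists a simple two-group comparison (Student or Mann-Whitney) with no centre term.

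Design of RIPOSTE Trial takes patients "from 3 centers in Northeastern France (CHRU Nancy, Institut Lorrain de Canérologie and HIA Legouest Metz". The abstract gives the size: "This is a prospective randomized controlled trial including 24 patients with invasive BC who have just undergone surgery". Recruitment and Randomization has patients "randomly assigned to one of the 2 groups based on a 1:1 principle using automatic software".

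Delivery is organised differently from recruitment. Sample Size says: "The 2 fencing halls have a maximum capacity of 24 patients per year (12 patients per hall". Interventions describes sessions in which "a group of 10–12 patients practiced adapted fencing", and Month 6 Visit refers to 2 fencing masters. The article does not say how the three hospitals map to the two halls.

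**The concern.** A random effect treats the centres as a sample from a population and estimates a variance from them. Three centres give 2 degrees of freedom for that variance, however many patients or visits each contributes. The Month 3 measurement adds information within patients but adds no centres.

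The explanation in Quantitative Analysis is about the effect of the intervention differing by centre. A random intercept describes something else, namely centres differing in their average level. If the arm effect itself is random over centres, it has to be judged against its variation over three centres. The fitted model may then test the arm on about 2 degrees of freedom, or estimate the variance at zero and so lose the term. Which of these happens depends on chance and on software settings. At stake is whether a main analysis of this pilot, whose results are meant to size the larger trial, has a predictable standard error and power.

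**Working it through.** **Inputs from the article.** 24 patients, 1:1, so 12 per arm; 3 centres; standard deviation 10, alpha 5%, power 80% (Sample Size).

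**Assumptions.** Equal split, so 8 patients per centre and 4 per arm per centre; 10 points taken as the standard deviation of change (the article gives it for the QoL score); two-sided test; one change value per patient.

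**The plan's own figure.** Sample Size states a detectable difference of 8.26 points. A two-sided t test gives 8.26 with 24 patients per arm. With 12 per arm it gives 11.97. That is a separate matter; about 12 points is used below because it is the difference that 12 per arm detects with 80% power.

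**Step 1: standard error.** Let tau be the standard deviation of the arm effect over centres. The arm difference within one centre has variance tau² + 2 × 10²/4 = tau² + 50. Averaged over 3 centres, the standard error is √((tau² + 50)/3), which is 4.08 at tau = 0.

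**Step 2: how often the centre-by-arm variance is estimated at zero.** This happens when its mean square does not exceed the residual mean square, which has 24 − 6 = 18 df. The probability is P(F(2,18) < 50/(50 + tau²)), and for 2 numerator df P(F < x) = 1 − (1 + 2x/18)^(−9).
- tau = 0: x = 1, giving 1 − 1.111^(−9) = 0.61.
- tau = 5: x = 50/75 = 0.667, giving 1 − 1.074^(−9) = 0.47.

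Simulation of 200,000 trials agrees (0.614 and 0.476). With true tau = 5, the central 95% of estimates of tau runs from 0 to 15.

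**Step 3: power at 12 points with tau = 0.**

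| Handling | Power |
|---|---|
| Variance bounded at zero, 2 df always | about 10% |
| Variance not bounded, 2 df (critical t 4.30) | 38% |
| Variance bounded, 20 df when the estimate is zero, otherwise 2 | about 50% |
| Variance bounded, 20 df always | about 71% |
| Centre fixed and additive, 20 df | 80% |

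The second and last rows are from the noncentral t distribution, the others from simulation. For the unbounded 2-df test, the detectable difference at 80% power is 23.1 points.

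**Step 4: if only a random intercept is meant.** Each centre has 8 patients, and the probability of a zero estimate is P(F(2,21) < 1/(1 + 8 × ICC/(1 − ICC))).
- ICC 0.05: x = 1/1.421 = 0.704, probability 0.49.
- ICC 0.10: x = 1/1.889 = 0.529, probability 0.40.

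With both arms in every centre, the arm is compared within centre, so its test stays near 20 df and changes little.

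**Step 5: centre as a fixed factor.** Residual df are 24 − 1 − 1 − 2 = 20. The detectable difference is 12.02 points, against 11.97 on 22 df without centre.

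**The case against.** The strongest reply is that the specification itself says only random centre effects. The centre-by-arm reading comes from one explanatory parenthesis, and a condensed article commonly leaves the covariance structure and the df method to the analysis plan. If a random intercept is meant, no serious loss of power follows, and a zero estimate simply returns the model without centre. This stands as a limit on the consequence. It does not remove the point, because the explanation the article does give describes an effect of intervention that varies by centre, and three levels are too few for either term.

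A second reply is that this is a pilot whose size was set by hall capacity, and that a simple two-group test is also listed under the main analysis. That is true, so the arm comparison does not rest on this model alone. The model is nevertheless part of the main analysis.

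A reader might also infer three stronger claims, which the documents do not support:
- *That the variance cannot be estimated at all.* Software will return a number. The trouble is that it is zero in roughly half of trials and very imprecise in the rest.
- *That power falls to one particular figure, such as 38%.* That value holds only for an unbounded variance tested on 2 df. The article fixes neither choice, so only a range can be given.
- *That hospital is the wrong unit and hall should replace it.* Group sessions in two halls make variation by hall plausible, but no passage links hospitals to halls, and centres may differ in patients or adjuvant care. A fixed hall main effect would also not capture an intervention effect that varies.

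**Conclusion.** The point holds in a limited form. As worded, Quantitative Analysis places in a main model a variance component with 2 df that 3 centres and 24 patients cannot usefully estimate. Taken literally as centre-by-arm, it is estimated at zero in about 61% of trials at tau = 0 and 47% at tau = 5, and power for 12 points with tau = 0 ranges from about 10% to 71%, against about 80% with centre fixed. Taken as an intercept, the variance is zero in about 40–49% of trials at ICC 0.10–0.05, with little effect on the arm test.

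These sizes rest on the equal split, the standard deviation of change of 10 and the chosen tau and ICC values, none of which the article states. The 2 df depend only on the number of centres.

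**What to change.** In Quantitative Analysis, replace the random centre effect by centre as a fixed additive factor (2 df), with patient as the only random or repeated unit. Remove the random intervention-by-centre term and the sentence that explains it. Show results by centre, and by hall since delivery may vary there, descriptively only.

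The change is to wording and one model statement. It spends 2 df, which moves the detectable difference from 11.97 to 12.02 points. Inference becomes conditional on these three centres. If the effect does vary, the fixed-centre standard error does not cover other centres: at tau = 5 the variance of the mean difference would be (25 + 50)/3 = 25, against 50/3 = 16.7 in the fixed model. The report should say so and leave generalisation over centres to the larger trial.
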